## 4. Conclusions

CARE-PF is the first study in Canada to provide robust epidemiological data on ILD. CARE-PF will also serve as a platform to support future translational and basic science research, with plans to establish biobanks that can be used to catalogue novel biomarkers to enable patient stratification, predict acute exacerbation risk, and monitor response to therapy. Finally, CARE-PF is designed to parallel other global initiatives, thus facilitating establishment of a global collaborative network that is essential for further advancement of pulmonary fibrosis research [4].

## Figures and Tables

**Figure 1 fig1:**
[figure not shown]
CARE-PF data sources and organizational structure. Copyright owned by the CARE-PF investigators. *∗* means Québec healthcare utilization data are available only for patients who are ≥65 years of age or on welfare.

**Table 1 tab1:** Eligibility criteria.

Inclusion criteria	(i) Fibrotic ILD of any subtype (ii) At least 18 years of age (iii) Able to provide informed consent (iv) Able to complete study questionnaires in English or French

Exclusion criteria	(i) None

**Table 2 tab2:** Schedule of study measurements.

Measurements	Baseline	Follow-up^**∗**^
Diagnostic criteria	X	+/−
Connective tissue disease serology		
HRCT: UIP pattern and favoured diagnosis		
Surgical lung biopsy: histological pattern		

Baseline clinical data	X	+/−
Demographics (e.g., age, sex, race)		
Smoking history		
Family history		
Medication exposures		
Occupational exposures		
Environmental exposures		
Comorbidities		

Symptoms	X	X
Dyspnea (UCSD SOBQ)		
Cough (visual analogue scale)		
Additional symptoms		

Quality of life	X	X
St. George's Respiratory Questionnaire		
European Quality of Life 5 Dimensions questionnaire		

Pulmonary function tests	X	X

6-minute walk tests	X	X

Additional measurements^**∗****∗**^	+/−	+/−

^*∗*^Follow-up data will be obtained when clinically indicated. Changes to diagnosis and baseline data will be recorded if applicable (e.g., a change in diagnosis and new comorbidity).

^*∗∗*^Additional measurements will be recorded when performed (e.g., echocardiogram, right heart catheterization, and bronchoscopy).

HRCT, high-resolution computed tomography; UIP, usual interstitial pneumonia; UCSD SOBQ, University of California San Diego Shortness of Breath Questionnaire.

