### 2.2. Study Participants

Consenting patients with incident or prevalent fibrotic ILD will be recruited from specialized ILD clinics at the University of British Columbia (Vancouver, BC), McMaster University (Hamilton, ON), University of Calgary (Calgary, AB), University of Toronto (Toronto, ON), and University of Montreal (Montreal, QC). Each of these institutions has dedicated ILD clinics in which patients are reviewed in a multidisciplinary setting with input from chest radiologists and lung pathologists to ensure that patients are accurately diagnosed according to established criteria [1, 14]. Our conservative recruitment estimate of 2,800 patients is based on historical volume at each ILD clinic, anticipating at least 160 prevalent cases per clinic in year 1 plus 80 incident cases in years 1 through 5. Additional sites may be added in subsequent years. All fibrotic ILD patients that meet eligibility criteria (Table 1) will be approached to determine their interest in participation. Patients with IPF comprise approximately 20% at each clinic, providing an expected IPF population of 560 patients.

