#### 2.5.3. Health Services Use

Patient-level data will be linked to respective provincial health administrative databases to capture inpatient, emergency department visits, and outpatient health services use. Consent to use provincial personal health numbers (PHNs) to link clinical and provincial data will be sought from all patients. Provincial data available for linkage are listed in Figure 1. All-cause and cause-specific health services use will be determined. Crude, age-, and sex-specific rates of health services use will be calculated.

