### 2.6. Statistical Analysis

The rate of change in FVC and DLCO will be determined using mixed effects models to account for nonstandardized follow-up schedules and patient dropout. Additional analyses will consider change in FVC as a dichotomous outcome (e.g., 5% and 10% absolute decline over 6–12 months). Subgroup analyses will be conducted for specific ILD subtypes and to compare the rate of physiological progression among subgroups. These analyses will adjust for potential confounders (e.g., age, sex, and baseline ILD severity), as well as additional variables identified on screening analysis.

The annual incidence of acute exacerbation of IPF will be determined within a population of patients with IPF. Subgroup analyses will be performed to determine the 1-year incidence of AE-IPF in patients with a new (incident) diagnosis of IPF, the annual incidence in subsequent years, and the incidence in patients with varying fibrosis severity. Similar analyses will be conducted in other fibrotic ILD subtypes. Outcomes following acute exacerbation will be reported as 30-day mortality, in-hospital mortality, median survival after exacerbation, and postsurvival quality of life. Multivariate analyses will be used to identify risk factors for acute exacerbation, as well as risk factors for mortality in patients experiencing exacerbation. Patients with multiple exacerbations will contribute only the first event to these analyses.

Healthcare services use and healthcare costs will be determined for ILD patients and for individual acute exacerbation events as described above. Healthcare services use and healthcare costs will be compared to a general non-ILD population. Disease controls will include patients with chronic obstructive pulmonary disease (COPD) and acute exacerbations of COPD. Four matched controls for each case will be identified from provincial databases, matching for age, sex, and geographic area of residence. Additional analyses will evaluate the change in health services use and healthcare costs in ILD patients over time and with changing lung function (e.g., stratified by mild, moderate, and severe ILD).

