## 3. Discussion

Previous studies have provided valuable data on the epidemiology, clinical features, and outcomes of fibrotic ILD; however these studies have methodological limitations. There is therefore an unmet need for a large well-phenotyped multicentre cohort that will allow detailed study of these populations in a Canadian healthcare environment.

The primary goal of CARE-PF is to improve our understanding of the natural history of fibrotic ILD subtypes and specifically to determine the incidence, risk factors, clinical features, and prognosis of acute exacerbation of IPF and other ILDs. Previous studies report an annual AE-IPF incidence of 5–15% per year [33]. Assuming 30% annual attrition, this incidence suggests that we would observe between 63 and 189 AE-IPF events during this 5-year study that includes 560 patients with IPF (2,800 total ILD patients). Our anticipated sample size will therefore allow detailed characterization of these important but uncommon outcomes. CARE-PF will include linkage to provincial health databases that will identify hospital admissions that are not captured in outpatient records at each ILD clinic. This will help identify events that were not reported to study investigators, thus increasing the sensitivity for identification of acute exacerbations and providing more accurate estimates of incidence and outcome.

A second goal of CARE-PF is to determine the impact of ILD and acute exacerbation of ILD on health services use and healthcare costs in a Canadian population. A recent study showed that healthcare costs are almost twofold higher in IPF compared to non-IPF controls [13]; however these findings are based upon potentially inaccurate ICD-10 coding and Medicare data that only applies to elderly patients in the United States. The single-payer structure of the centralized Canadian healthcare system will allow CARE-PF to address some of these limitations by linking well-characterized ILD patients to patient-specific provincial data that includes health services use and healthcare costs. CARE-PF is therefore ideally situated to determine the cost implications of fibrotic ILD, thus providing important data that can be used by stakeholders (patients, governments, industry, and healthcare leaders) to inform decisions on treatment, legislature, and research directions.

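### Linkage and 1:4 matching are specified for every case, but Québec utilisation data cover only patients aged 65 or over or on welfare, so under-65 Québec cases cannot get the stated comparator

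*Protocol article*

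**What the plan says.** The footnote to Figure 1 in the protocol article states that Québec "healthcare utilization data are available only for patients who are ≥65 years of age or on welfare".

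The methods carry no matching restriction:

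- Section 2.5.3 (Health Services Use) describes the linkage as follows: "Patient-level data will be linked to respective provincial health administrative databases to capture inpatient, emergency department visits, and outpatient health services use". The same section says that permission to use health numbers to "link clinical and provincial data will be sought from all patients". It refers to Figure 1 for the list of available data.
- Section 2.5.4 (Healthcare Costs) takes costs from the same province-specific sources and cross-references them with clinical records.
- Section 2.6 (Statistical Analysis): "Healthcare services use and healthcare costs will be compared to a general non-ILD population", with COPD patients as disease controls. It continues: "Four matched controls for each case will be identified from provincial databases, matching for age, sex, and geographic area of residence".

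Montreal is one of the five recruiting clinics (section 2.2), and the only age criterion in Table 1 is "At least 18 years of age". Québec patients aged 18 to 64 are therefore eligible.

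**The concern.** The article fixes the control source, the ratio and the matching factors. Its own footnote shows that in one of the four provinces this rule cannot deliver the comparator it names for cases under 65. Such a case, matched on age and area, can draw controls only from people on welfare. Welfare status is not a matching factor, and people on welfare are not the general population.

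The cases have a gap of their own. Those under 65 and not on welfare have no linked record, so their use can be known only from self-report and clinic records, which controls do not have.

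At stake is the registry's second goal, the effect of ILD on health services use and cost. Case-control differences and age-specific rates below 65 would combine provinces that observe different populations. This follows from how the data are selected, so a larger sample does not remove it.

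**Working it through.** **1. Planned size, to get the Québec share.** Inputs from section 2.2: five clinics, 160 prevalent cases per clinic in year 1, and 80 incident cases per clinic in each of years 1 to 5.

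- Per clinic: 160 + 5 × 80 = 560.
- All clinics: 5 × 560 = 2,800, which reproduces the stated cohort size.
- Québec share: 560 / 2,800 = 20%, if sites recruit equally, as the calculation in section 2.2 implies.

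**2. Patients who may lack linked data.** The article gives neither the share under 65 nor the share on welfare, so both are assumptions.

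Patients without linked use = 560 × (share under 65) × (1 − share of those on welfare)

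| Under 65 (assumed) | On welfare (assumed) | Patients | % of 2,800 |
|---|---|---|---|
| 30% | 0% | 168 | 6.0 |
| 30% | 20% | 134 | 4.8 |
| 50% | 0% | 280 | 10.0 |
| 50% | 20% | 224 | 8.0 |
| 60% | 0% | 336 | 12.0 |

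The 0% welfare rows are upper bounds for their age split.

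**3. Controls that cannot be found as described.** At four per case, 2,800 cases need 4 × 2,800 = 11,200 controls per comparison group. With 168–280 cases affected, 4 × 168 = 672 to 4 × 280 = 1,120 of these could not be non-welfare Québec residents of the case's age. The wider assumptions in the table (134–336 cases) give about 538–1,344.

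**4. What follows if the rule is applied as written to an under-65 Québec case.**

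| Case | Case's use observed through | Controls available | Result |
|---|---|---|---|
| On welfare | Linked data | Welfare recipients only | Alike on welfare, but not a general-population comparison |
| Not on welfare, linked data only | Nothing | Welfare recipients only | No usable comparison |
| Not on welfare, self-report and clinic records used | Self-report and clinic records | Welfare recipients, provincial data only | Populations and capture methods both differ between case and control |

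No row gives the comparison that section 2.6 describes. The COPD controls face the same limit if they come from the same data.

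**The case against.** The strongest reply is that the limit is disclosed and that section 2.5.3 points to the figure carrying it, so what remains is analysis-set handling that a condensed article may leave to the full protocol. The disclosure is real. However, the article goes on to fix a matching rule for each case that its footnote makes unworkable for some of them, and the limitations paragraph of the Discussion does not mention it. That is a conflict between stated elements, not an omitted detail.

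A second reply also has force: a non-welfare case without a linked record adds no linked cost, and under-65 Québec cases that are linked are on welfare, as their controls would be. In a linked-only analysis the problem is therefore mainly one of representativeness. A distorted contrast arises if self-report or clinic-record costs are brought in for cases, and the article does name those sources.

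A reader might infer more than the document supports:

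- *All under-65 Québec use is lost.* It is not. Welfare recipients are in the data, use is also self-reported (section 2.1), investigators record hospitalizations (section 2.5.2), and cost data are cross-referenced with clinical records (section 2.5.4).
- *Unlinked patients will be counted as zero users.* Nothing in the article says so.
- *The registry repeats the weakness it criticises in US data.* The Discussion faults "potentially inaccurate ICD-10 coding and Medicare data that only applies to elderly patients in the United States" but claims only to address some of these limitations, and four of the five sites lie outside Québec.
- *Acute exacerbation incidence is compromised.* Québec would supply about 20% × 560 = 112 IPF patients, of whom 34–56 would be under 65 at 30–50%. Their events can still reach central adjudication through investigator records. Linkage adds sensitivity, and only that addition is in doubt.

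Finally, Figure 1 is not shown, so which Québec entries carry the asterisk cannot be checked. The footnote's wording covers utilisation data generally, but whether hospital, physician and drug data are equally restricted is unknown.

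**Conclusion.** The concern holds in limited form. The footnote and the linkage and matching rules conflict for Québec patients under 65. Those not on welfare lack administratively linked use, and under-65 controls found in the restricted data would be welfare recipients instead of members of the general non-ILD population.

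The size is up to 168–280 patients (6–10% of the cohort) at an assumed 30–50% under 65, fewer after removing those on welfare. This also assumes equal site recruitment, that Montreal clinic patients live in Québec, and that the footnote applies to the databases used for the comparison. The direction and size of any bias in costs cannot be derived from the document.

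Severity is moderate: the second goal is mainly affected, and the effect on exacerbation ascertainment is secondary and possible only.

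**What to change.** Reconcile the Figure 1 footnote with sections 2.5.3, 2.5.4 and 2.6:

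1. Restrict the linked utilisation and cost comparison in Québec to one defined population with complete data, for example those aged 65 or over. Apply it identically to cases, general-population controls and COPD controls.
2. State that use without linkage is treated as not observed.
3. Label under-65 linked rates and costs as coming from British Columbia, Alberta and Ontario only.
4. State that the gain from linkage in finding missed admissions may not apply to Québec patients under 65 and not on welfare.
5. State which Québec databases the restriction covers.

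The cost is analysis-set wording and a modest loss of Québec patients from the linked analyses. With an age limit of 65, that loss includes the under-65 welfare recipients, whose linked data do exist. They stay in all other registry analyses.
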